## Abstract

**Background:**

Although a device is needed to continuously measure blood glucose levels within an intensive care setting, and several large-scale prospective studies have shown that patients might benefit from intensive insulin, potassium, or glucose therapy during intensive care, no devices are currently available to continuously assess blood glucose levels in critically ill patients. We conceived the study described here to evaluate the clinical use of the Continuous Glucose Monitor (CGM) performed via a central vein, and to determine the impact of phenomena, such as drift and shift, on the agreement between the CGM and a RAPIDLab® 1265 blood gas analyser (BGA).

**Methods/design:**

In the CONTinuous ASSessment of blood GLUcose (CONTASSGLU) study, up to 130 patients under intensive care will be fitted with the CGM, an ex vivo device that continuously measures blood glucose and lactate levels. Readings from the device taken 8 h after initial placement and calibration will be compared with values measured by a BGA. For this study, we chose the BGA as it is an established standard point-of-care device, instead of the devices used in certified central laboratories. Nevertheless, we will also independently compare the results from the point-of-care BGA with those determined by a central laboratory-based device. Blood samples will be collected from each patient from the same site in which the CGM will measure blood glucose. Consequently, each participant will serve as their own control, and no randomisation is necessary. The 95% limits of agreement and the corresponding confidence intervals will be calculated and compared with a prespecified clinically acceptable relative difference of 20%.

**Discussion:**

Several attempts have been made to develop a device to continuously measure blood glucose levels within an intensive care setting or to use the devices that were originally designed for diabetes management, as several of these devices are already available. However, none of these devices were successful in intensive care settings. CONTASSGLU may well bridge this gap by confirming the ability of the CGM to continuously measure blood glucose levels in intensive care settings.

**Trial registration:**

ClinicalTrials.gov NCT01580176

## Background

TRACE Analytics GmbH (Braunschweig, Germany) and Mechatronic AG (Darmstadt, Germany), in a joint effort with the University Hospital Heidelberg (Germany), recently developed the Continuous GlucoseMonitor (CGM), an *ex vivo* device that continuously measures blood glucose and lactate levels. The CGM assesses blood glucose levels from a microdialysate of the circulating blood by an amperometric technique. It consists of a control unit and a sensor system with a sampling device.

Critically ill patients under intensive care, including patients with severe sepsis/septic shock, may have severe microcirculatory disturbances. These disturbances may cause tissue hypoxia [1]. Critically ill patients may also have metabolic disturbances, including hyperglycaemia or insulin resistance, even if they did not previously have diabetes [2,3]. Another common metabolic disturbance is acidosis, which may severely impair endothelial function [4]. Tissue hypoxia and respiratory acidosis may worsen this condition. Additionally, insulin resistance or insulin deficiency may induce metabolic acidosis [5]. If endothelial function to retain blood plasma is lost [6] fluid loss from the circulation may further diminish capillary blood flow [1]. The microcirculatory disturbances may maintain themselves and ultimately lead to death [7].

The sensor technology (i.e., the control unit and the sensor system) was confirmed to be functional in preliminary laboratory and preclinical tests via peripheral intravenous access to the vascular bed. However, it is not known whether these promising results also apply to central venous access.

Excess fluid loss may cause severe interstitial oedema [6], characterised by swelling of the face, body, and extremities. Oedema may also render peripheral intravenous access technically impossible for patients under intensive care, necessitating an alternative route.

### Objectives

The objective of the CONTinuous ASSessment of blood GLUcose (CONTASSGLU) study is to evaluate the clinical use of the CGM performed via a central vein, and to determine the impact of phenomena, such as drift and shift, on the agreement between the CGM and a RAPIDLab® 1265 blood gas analyser (BGA). To fulfil this objective, up to 130 patients under intensive care will be fitted with the CGM. Readings from the device taken 8 h after initial placement and calibration will be compared with values measured by a BGA.

## Methods/design

### Study design

CONTASSGLU is a prospective clinical study that is designed to assess the level of agreement between two devices used to measure blood glucose. Readings from the CGM will be compared with values measured by a BGA, an established device in clinical care. Blood samples used for the BGA measurement will be collected from each patient from the same site and at the same time at which the CGM will measure blood glucose. Consequently, each participant will serve as their own control, and no randomisation is necessary.

### Participants

Considering that patients with severe sepsis/septic shock cannot give written informed consent, and we could not justify asking the patient’s next of kin for written consent, we did not use this population of patients. Instead, we plan to enrol patients who are scheduled for major abdominal surgery, predominantly pancreatic surgery (pancreatectomy), for any reason and who are expected to be under intensive care for ≥ 8 h after surgery.

We will primarily focus on patients undergoing pancreatectomy for any reason (total or subtotal/distal pancreatectomy) to assess the level of agreement between the two devices over a wider range of blood glucose levels than would be possible in other groups of patients. The pancreatic islets of Langerhans provide critical control of blood glucose homeostasis. Consequently, blood glucose levels are expected to reach pathological values (i.e., dysglycaemia) immediately after pancreatectomy. Because the islets of Langerhans are mainly located in the pancreatic tail [8], patients undergoing total pancreatectomy or subtotal pancreatectomy (i.e. distal pancreatectomy) will be considered for admission to the study. Table 1 provides a comprehensive list of the eligibility criteria to be applied in this study.

**Table 1 T1:** Eligibility criteria

**Patients meeting all of the following criteria will be considered for admission to the study:**
· Undergoing major abdominal surgery, predominantly pancreatic surgery (pancreatectomy), for any reason
· Require careful postoperative monitoring of blood glucose levels
· Expected to be under intensive care for ≥ 8 h after surgery
· Insertion of a multi-lumen central venous catheter for medical reasons (e.g., anaesthesia and operative purposes)
· Aged 18–80 years
· Able to understand the design and possible consequences of the clinical study
In addition, all patients must meet the following criteria, or will not be included in the study:
· Successful central venous cannulisations with a multi-lumen catheter
· One lumen is not needed for medical purposes, such as perioperative fluid therapy or medication administration
Patients fulfilling any of the following criteria will be excluded from the study:
· History of thrombosis, embolism, or vascular obliteration
· Bleeding disorders (e.g., thrombocytosis)
· Acute or chronic cardiac failure
· Acute or chronic kidney failure (i.e., patients on renal replacement therapy)
· Evidence of postoperative hyperhydration (pulmonary vascular congestion)
· Acquired immune deficiency syndrome
· Receiving immunosuppressive therapy
· Signs or symptoms of acute or chronic infection
· No perioperative antibiotic prophylaxis (with mezlocillin 4 g and metronidazole 500 mg, for example)
· No perioperative prophylaxis to prevent venous thromboembolism (e.g., unfractionated or fractioned/low-molecular weight heparin)
· The amount of flushing medium administered is > 500 mL
· Pregnancy or lactation
· Participation in other clinical studies and observation period of competing studies, respectively

No patient will be allowed to enrol in this study more than once.

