### Primary outcome measure

The primary outcome measure, referred to as the agreement at point of care, is defined as the level of agreement in blood glucose levels determined by the CGM and a BGA, assessed 8 h after the initial placement and calibration of the CGM.

The agreement for the *i*th patient will be quantified as the relative difference $d_{i}$ between readings ($y_{\mathrm{gi}}$) and measurement results ($y_{\mathrm{ri}}$), calculated as $d_{i}=\frac{2\left(y_{\mathrm{gi}}-y_{\mathrm{ri}}\right)}{y_{\mathrm{gi}}+y_{\mathrm{ri}}}$. Using the approach suggested by Bland and Altman [9,10] the limits of this agreement are set to $\bar{d}\pm 2s_{d}$, where $\bar{d}$ and $s_{d}$ are the empirical mean and the standard deviation of *d*_*i*_.

According to the guidelines for quality assurance in quantitative laboratory tests issued by the German Medical Association (GMA) [11,12], the measurement results from any device should not differ from an established standard by more than 15%. In this setting, however, the standard is not an unknown clinical value measured with a standard device but instead a prepared sample for which accuracy was achieved by titration or other methods. Unlike this method, the test–retest variance of the standard device contributes to the total error in our study. Moreover, the asymmetrical measure $\frac{1}{y_{0}}\sqrt{\frac{1}{n}{\left(y_{i}-\;y_{0}\right)}^{2}}$ is smaller than the measure $\left|\bar{d}\right|\pm 2s$ taken from the symmetrical limits of agreement under any but highly unlikely conditions. Thus $\bar{d}\pm 2s_{d}$ has been set to 20%, which is more conservative than the requirements imposed by the GMA. Therefore, the agreement at point-of-care is considered sufficient if the limits of agreement of the relative difference and their 95% confidence intervals (CIs) are within 20%.

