### Measurement process

All subjects will first enter a screening stage lasting up to 1 month, and an additional 2-h reference period before the study period. The study will consist of a 24-h measurement period and a 48-h follow-up period. During the measurement period, blood samples will be obtained 13 times. The overall duration of the measurement stage will be determined by the duration of intensive care.

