### Screening (Visit 1)

All patients admitted to University Hospital Heidelberg will be assessed for eligibility after being fully informed of all aspects of the study that are relevant to their decision to participate. Patients will be asked to sign and date an informed consent form [19]. After providing consent, the subjects will undergo screening, which will involve assessment of baseline characteristics and medical history (Table 2).

**Table 2 T2:** Study timetable

	**Visit 1**	**Visit 2**	**Visit 3 - 9**	**Visit 10**	**Visit 11 -12**	**Visit 13**	**Visit 14**	**Visit 15**
	up to one month and a reference period^1^ of 2 h before Visit 2	0 h^2^	1–7 h (every hour) ± 5 min	8 h ± 5 min	9 and 10 h ± 5 min	16 h ± 30 min	24 h ± 30 min	72 h ± 1 h
Informed consent	●							
Eligibility criteria	●	●						
Medical history	●							
Concomitant medication	●	●	●	●	●	●	●	●
Physical examination	●						●	
Vital signs^3^	●	●	●	●	●	●	●	●
Pregnancy test^4^	●							
Placement of the CGM		●						
CGM calibration		●						
Continuous glucose and lactate monitoring		●	●	●	●	●	●	up to every 2 h
Recalibration				●				
Central venous blood sampling for the BGA^5^			●	●	●	●	●	
Central venous blood sampling for central laboratory measurement^6^		●		●		●	●	
Removal of CGM								●
Assessment of unwanted events/effects		●	●	●	●	●	●	●

^1^ Priming, tempering and transient oscillation of the sensor systems.

^2^ Within 2 h of transfer to the recovery room or intensive care unit.

^3^ Heart rate, blood pressure, and tympanic body temperature.

^4^ Only females with reproductive potential.

^5^ Samples used to assess blood glucose, blood lactate, haematocrit, and haemoglobin.

^6^ Samples used to assess blood glucose and blood lactate levels.

CGM: continuous glucose monitor; BGA: blood gas analyser.

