### Study period (Visits 2–14)

All subjects will be treated according to the local standards at the University Hospital Heidelberg. After successful induction of anaesthesia, a multi-lumen central venous catheter will be implanted in all patients. Perioperative antibiotic prophylaxis (e.g., 4 g mezlocillin and 500 mg metronidazole) will be administered approximately 30 min before commencing surgery, and will be repeated if the duration of surgery exceeds 4 h. Perioperative prophylaxis with unfractionated or fractionated/low-molecular-weight heparin will be administered to prevent venous thromboembolism. Patients will be closely monitored throughout surgery and the post-operative period.

Within 2 h after transfer to the recovery room or an intensive care unit, the patients will be re-assessed for eligibility and the planned measurements will be commenced, as summarised in the Figure 1 and Table 2. Unless medical reasons preclude entry into the study (i.e., a lumen is not required for medical purposes, such as perioperative fluid therapy and medications) the patients will be fitted with the CGM according to the manufacturer’s instructions. The device is to be primed, connected to the patient, and referenced to the blood glucose level measured by a BGA. This point represents the start of the measurement period (1 h before the first measurement).

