**Figure 1 F1:**
[figure not shown]
**Timeline.** PC: Priming and Calibration Period (Priming, tempering, transient oscillation and initial calibration of the sensor from the Continuous GlucoseMonitor); R: Referencing; Rec: Recalibration (duration = 10 min including washing); M: Glucose and Lactatemonitoring; B: Blood sampling for comparison (glucose, lactate, haemoglobin, haematocrit); L: Blood sampling for central lab (glucose and lactate).

For the next 10 h, the patients will be visited by the research staff every hour. At each visit, the CGM value will be recorded and blood samples will be collected for measurement by a BGA. At 0 and 8 h (Visits 2 and 10, respectively), additional blood samples will be collected and measured using the ADVIA 2400 Chemistry System to independently confirm the blood glucose measurement. Using the value obtained at 8 h (Visit 10), the CGM will be re-calibrated and further values will be recorded at 9, 10, 16, and 24 h. At 16 and 24 h (Visits 13 and 14, respectively), additional blood samples will be collected. Visit 14 represents the end of the measurement period. The CGM is left in place until Visit 15.

No subjects will be fitted with the CGM unless central venous cannulisation was necessary for medical reasons. The central venous catheters will be removed when clinically indicated. No subjects will be equipped or re-equipped with central venous catheters unless there is a clear medical reason. If discharge from the recovery room or intensive care unit occurs within 24 h, Visit 14 will be brought forward and the CGM will be removed.

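### The expected-stay criterion is counted from surgery but the primary reading from device placement, so an eligible patient can be discharged before the 8-h primary pair exists

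*Protocol article*

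**What the plan says.** - **Entry.** Table 1 (Eligibility criteria) requires patients to be "Expected to be under intensive care for ≥ 8 h after surgery". The Participants section repeats this, also counted from surgery.
- **Primary outcome.** Agreement between the CGM and the blood gas analyser is "assessed 8 h after the initial placement and calibration of the CGM" (Primary outcome measure). Table 2 places this at Visit 10, with a window of ± 5 min.
- **Time zero.** Table 2, footnote 2, puts Visit 2 (placement and calibration) at "Within 2 h of transfer to the recovery room or intensive care unit". The Study period section starts the clock once the device has been primed, connected and referenced: "This point represents the start of the measurement period (1 h before the first measurement").
- **Re-check.** "Within 2 h after transfer to the recovery room or an intensive care unit, the patients will be re-assessed for eligibility" (Study period). No stay requirement counted from placement is stated there.
- **Early discharge.** Where "discharge from the recovery room or intensive care unit occurs within 24 h, Visit 14 will be brought forward and the CGM will be removed" (Study period, text after Figure 1). The Measurement process section adds: "The overall duration of the measurement stage will be determined by the duration of intensive care".
- **Reserve and missing data.** Up to 130 patients are enrolled to obtain at least 100 pairs (Sample size). A linear mixed model on the differences up to 8 h is used to impute missing data (Statistical methods).

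**The concern.** The two 8-h periods start from different events, and the one that governs entry starts first. A patient can satisfy the entry criterion exactly as written and still leave intensive care before the primary pair is due. The discharge rule moves Visit 14 forward, so a last pair may be taken on leaving, but it does not stand in for the 8-h pair of Visit 10.

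What is at stake is avoidable loss of the primary value. Each lost pair uses up part of the margin between 130 enrolled and 100 needed. Where the value is imputed, it is projected from earlier hours, whereas the study's objective includes measuring drift and shift, and the primary criterion depends on both the mean and the spread of the differences at 8 h. The patients affected are by construction those with the shortest stays, so the loss may be informative.

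**Working it through.** **1. The protocol's own power figure.** Inputs from the Sample size section: λ = 20%, δ = 5%, σ = 6%, n = 100. Statistical methods gives a one-sided test at 0.05.

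- Threshold: −(1.645 + 0.842) = −2.486, as stated.
- Standardised distance: (5 + 2 × 6 − 20) / √(3 × 36 / 100) = −3 / 1.039 = −2.887. Power = Φ(2.887 − 1.645) = 89.3%, so the claim of more than 80% holds.
- Smallest n for 80% power: 3 × 36 × 2.4865² / 9 = 74.2, so 75 pairs.

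**2. The timeline.** Let D be the placement delay after transfer (0 to 2 h). The primary reading falls at D + 8 h after transfer, ± 5 min.

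| Placement after transfer | Primary reading after transfer | Shortfall against an 8-h stay |
|---|---|---|
| 0 h | 8 h | 0 h |
| 0.5 h | 8.5 h | 0.5 h |
| 1 h | 9 h | 1 h |
| 1.5 h | 9.5 h | 1.5 h |
| 2 h | 10 h | 2 h |

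Any time between the end of surgery and transfer adds to the shortfall. With placement at 2 h, an 8-h stay ends at device hour 6, so the last scheduled pair is the 6-h one.

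Let X be the stay beyond 8 h. The primary pair is lost when D > X.

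**3. How many patients (assumption).** The article gives no length-of-stay figures. Assume X is exponential with mean m, and treat end of surgery and transfer as simultaneous.

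- All devices placed at 2 h: loss = 1 − exp(−2/m).
- Placement uniform over 0 to 2 h: loss = 1 − (m/2)(1 − exp(−2/m)).

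| m | Placed at 2 h | of 130 | Uniform 0–2 h | of 130 |
|---|---|---|---|---|
| 8 h | 22.1% | 29 | 11.5% | 15 |
| 16 h | 11.8% | 15 | 6.0% | 8 |
| 24 h | 8.0% | 10 | 4.1% | 5 |

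**4. Against the reserve.** 130 − 100 = 30 spare patients, so the target tolerates 30/130 = 23.1% loss from all causes together. The scenarios use 5 to 29 of those 30. The worst leaves 130 − 29 = 101 pairs.

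**5. Against power, at δ = 5% and σ = 6%.** The same formula, for total loss from any cause:

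| Loss | Pairs | Power |
|---|---|---|
| 10% | 117 | 93.0% |
| 20% | 104 | 90.3% |
| 30% | 91 | 86.6% |
| 40% | 78 | 81.7% |
| 50% | 65 | 75.3% |

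Power stays at 80% down to 75 pairs, a loss of 55/130 = 42%.

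**The case against.** The strongest case is that the mismatch is small and may hardly matter.

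- **The 2 h is an upper limit.** A patient who stays 9 h and is fitted at 0.5 h supplies the reading at 8.5 h. A reader might infer that everyone staying 8 to 10 h is lost. The documents do not support that: the pair is lost only if the delay exceeds the stay beyond 8 h. Nor should the 2-h reference period in Table 2 be added to make a 4-h gap, because it is sensor preparation before Visit 2 and can run before or alongside transfer. This stands.
- **The criterion is a forecast and a minimum.** Readings at 16 and 24 h and a device left in place until Visit 15 show that longer stays are planned for. This stands, and the true loss may be small. The upper scenario fits the schedule poorly: with m = 8 h only exp(−16/8) = 14% of patients would still be in care at 24 h, and with m = 24 h, exp(−16/24) = 51%.
- **The target survives.** Even the worst scenario leaves 101 pairs. This stands for early discharge alone. It leaves one spare patient for every other cause of loss.
- **Informative loss is not shown.** A reader might infer that the values are missing not at random. The documents do not link speed of recovery to disagreement between the devices, and the hourly pairs before discharge feed the imputation model. Only the possibility can be claimed.

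None of this removes the mismatch. The Visit 2 re-assessment would close the gap only if it were read as a new 8 h from placement, and the criterion says after surgery.

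**Conclusion.** The point holds as a mismatch of up to about 2 h between the entry criterion and the primary outcome's clock, plus any time from the end of surgery to transfer. Nothing in the article protects the 8-h reading from early discharge.

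The timing conclusion rests only on the protocol's stated times. The 4% to 22% range rests on an assumed exponential remaining stay and on two assumed placement patterns; its upper end also needs every device to be placed at the 2-h limit. The actual number affected is unknown.

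A reader might go further and conclude that the study is underpowered or will miss 100 pairs. The figures do not show that. The case for change is that the loss of the primary value is avoidable, and that imputing it from earlier hours weakens the evidence at the time point the study was set up to test. It is worth correcting but does not invalidate the design.

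**What to change.** Count the expected stay from the primary outcome's own clock. Reword the criterion in Table 1, and its counterpart in the Participants section, to: *expected to remain under intensive care for at least 8 h after CGM placement and calibration*. Confirm it at the Visit 2 eligibility re-assessment, which is already scheduled just before fitting.

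A fixed rule of 10 h after transfer should not be used instead. It is not equivalent, because 8 h after placement means 8 to 10 h after transfer, and it would exclude promptly fitted patients who could supply the primary pair.

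The cost is a one-line change with no added procedure. The downside is that a few patients with a short expected remaining stay are not fitted, including some who might have stayed longer than forecast. Because stay is only forecast, the change reduces the loss but cannot remove it.

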### Study settings

The Department of Anaesthesiology, at University Hospital Heidelberg, Heidelberg, Germany will be responsible for recruiting, treating, and following all patients in this study. The department will be monitored by the Coordination Centre for Clinical Trials, which will be responsible for study management, medical device safety, data management, and statistical analyses.

